**Discussion:**

The positive outcomes and user experience of VR-CBT will advance researches on the effectiveness of psychosocial interventions that aims to promote adaptation to the unexpected sick role on cancer populations. This protocol can be tested as an accessible and feasible alternative to traditional high-cost treatment in a randomized controlled study to improve the outcomes of younger cancer survivors.

Trial registration.

The protocol was registered on 21 June, 2023 in Chinese Clinical Trial Registry (No.: ChiCTR2300072699) at https://www.chictr.org.cn/.

## Background

Globally, colorectal cancer (CRC) is the third most commonly diagnosed cancer and the second major cause of cancer death in both sexes [1]. In 2020, newly diagnosed CRC patients in China occupied 28.8% of all new cases worldwide [1]. Although CRC typically affects older populations, the onset age of the disease has been getting younger [2]. A body of international literature reveals that there has been an observed rise in the prevalence of CRC among younger adults under the age of 50 of both sexes, constituting approximately 10% of the total new cases of CRC reported [2, 3]. Poorer differentiation, more advanced stage, and worse prognosis are typically witnessed in younger patients with CRC [3]. Further, they may experience psychosocial impairment due to bowel dysfunction, urinary problems, sexual dysfunction, and the possibility of an ostomy following rectal resection[4].

The prevalence of CRC among the younger population sparked a concern that CRC patients at working age would confront an undesirable role—being young and sick—that conflicted with their stage of life and their crucial roles as the backbone of their nuclear and extended family [5, 6]. It is reported that people diagnosed during their working years have lower quality of life (QOL), more practical problems, and worse psychosocial consequences than older-onset CRC patients aged over 60 [2, 7]. This might be as a result of the numerous difficulties working-age CRC patients face, who are managing multiple roles at the same time as taking on the role of a cancer patient at an unexpectedly young age, suffering more detrimental and maladaptive psychosocial effects than their older counterparts [7]. It has been demonstrated that cancer-related identities are associated with adjustment, particularly psychological well-being [8].

In the sociological literature, illness refers to an incapacity of an individual to effectively perform social roles [9]. Talcott Parsons [10] emphasized that the sociocultural context in which disease occurs allows for the definition of a particular social role—the sick role—that people may occupy during a period of illness. The sick role is the core patient role within the medical system and is considered an irregular or dysfunctional societal role [11, 12]. Suffering, helplessness, disability, and the risk, or even certainty of death following diagnosis and treatment represent profound disruptions to the prior role expectations [10]. It is therefore challenging for patients to adjust to the unexpected sick role, especially for those in their young and middle adulthood with limited illness experience and less effective coping strategies first encountered with surgery. The sick role adaptation refers to regulation of self-identity, accommodation of cognitive and behavioral responses following the diagnosis [13]. In other words, inappropriate cognitions, emotional states, and overt conducts associated to disease are all important concomitants of the sick role maladaptation [14].

Commonly reported experiences of CRC patients during the preoperative stage include fear, helplessness, isolation, devastation and uncertainty [15, 16]. Postoperatively, CRC patients are confronted with multifaceted psychological challenges include severe anxiety and depression, embarrassment, loss of dignity, as well as worse social and emotional role functioning till 4–6 weeks after surgery [16–19]. To deal with these stressful and traumatic challenges, patients with CRC need to make major psychosocial adaptations [20]. Therefore, it is noted that technology-based interventions are proposed to deliver preoperatively to facilitate CRC patients to accept their diagnosis and adjust to life following surgery [16]. Patients must incorporate their cancer experience into their self-concept required by the uncertainty and chronicity of cancer. This may be especially essential for people who are diagnosed with cancer while they are still in their working age because they must complete normal developmental tasks such as identity formation, intimate relationships, and financial independence in addition to managing their cancer treatments [8]. However, to date, previous studies focused on psychosocial interventions for CRC patients have not dealt with the issue of sick role adaptation.

A literature review showed that cognitive behavioral therapy (CBT) was one of the most common and effective intervention in improving QOL and alleviating adverse psychological effects among CRC survivors [20]. One explanation could be that CBT interventions for patients cover a wide variety of aspects, including social, psychological, and physical components, which can enhance QOL and alleviate negative psychological impacts [21]. However, the requirement for experienced practitioners and the time as well as the resources required to prepare one, hinders the widespread adoption of CBT in general practice [22]. With the growing proliferation of smartphones, CBT delivered by mobile application (app) becomes an attractive option since it is cost-effective and highly accessible. Interventions built upon CBT principles and delivered via a mobile app has been shown to be as effective as face-to-face CBT with stronger benefits in cancer patients [22, 23].

The development of virtual reality (VR) technology provides full control over the user experience, which can be used therapeutically to alleviate some of the negative effects of illness by enabling people to "escape" from their real world to pleasant environments where they can have more positive thoughts and feelings [24, 25]. This tool has shown several advantages that are noteworthy for optimizing psychotherapies including its versatility, acceptability as well as adherence to treatment [26]. Because of these advantages, VR-based therapy has been developed and applied to evaluating and treating various psychological issues [27]. The majority of previous studies on VR-based therapies for cancer patients have focused on reducing anxiety, fatigue and pain [28–30]. For many existing CBT procedures, VR has been regarded a therapeutically appropriate treatment modality, and for its more experiential component, VR-based approaches may increase the possibility of transferring knowledge and skills gained during VR sessions to patients’ everyday life [25, 26]. Since VR can be used frequently, delivering CBT techniques such as breath relaxation with VR can enhance its effectiveness [31]. There is ample evidence to support efficacy of VR-based interventions in psychotherapy and cancer populations with improved emotional, cognitive, and physical well-being [32, 33], there is, however, a striking lack of VR-based CBT therapies for CRC patients. As a result, it is necessary to develop a self-led VR-based CBT intervention on the sick role adaptation among working-age CRC patients and explore its effectiveness.

The Common Sense Model of Self-regulation (CSM) is probably the most prevalent theory to explain and predict how patient adapt to their disease and behave [34]. According to CSM, an understanding of adaptability to health threats originates in an analysis of threat from the lay perspective of the individual, in particular, is essential for initiating subsequent coping strategies aimed at both threat and emotion management. These two simultaneous processes constitute a self-regulatory system with substantial consequences for illness outcomes such as adaptation to illness [35]. Previously, the combination of CSM and CBT technique has been applied in patients with chronic disease [34]. CBT is therefore proposed as a potentially beneficial approach to improve the sick role adaptation among CRC patients by reconstructing their beliefs of CRC, adjusting negative emotions and adopting effective coping strategies. Based on CSM and CBT technique, emotion, cognition, and coping were the basis for the development of the intervention strategies in our study, and CBT techniques of cognitive reconstruction and behavioral training were incorporated throughout the entire intervention as technical tools. This intervention targeted towards negative emotions, irrational illness perception, and maladaptive coping strategies thereby helping working-age CRC patients to adapt to the sick role. The causal model of this study is presented in Fig. 1.

**Fig. 1 Fig1:**
[figure not shown]
The causal model of this study

This study aims to develop a study protocol for a self-led VR-based CBT intervention to facilitate the sick role adaptation, modify irrational illness cognition, alleviate anxiety and depression, and improve QOL among working-age CRC patients and to evaluate its effectiveness.

## Hypotheses

We hypothesize that that working-age CRC patients in the VR-CBT group, in comparison with participants assigned to the attention control (AC) group, will report significantly better adaptation to the sick role, more rational illness cognition, lower levels of anxiety and depression and better QOL, at 1, 2 and 3-month after the intervention.

### Study design

A single center, parallel mixed-methods, assessor-blinded, randomized controlled trial will be conducted to investigate the effect of VR-based CBT on the sick role adaptation in working-age CRC patients with colorectal cancer. The protocol will adhere to the SPIRIT 2013 Statement guidelines for designing and reporting RCTs [36]. This study was registered on 21 June, 2023 in Chinese Clinical Trial Registry (No.: ChiCTR2300072699) at https://www.chictr.org.cn/.

### Sample/participants

The participants will be recruited from patients admitting to colorectal surgery ward with 70 beds at a tertiary-A cancer center in Guangzhou, Guangdong province, which is the largest integrated cancer center in the southern China.

Patients will be involved in the study if they: (1) are 18 ~ 59 years old, considering the retirement age can be no later than 60 in China, where people over this age are generally considered the elderly [37, 38]; (2) have been diagnosed with primary colon cancer or rectal cancer staging I-III in the past 3 months; (3) are informed diagnosis; (4) are able to comprehend spoken Mandarin and read Chinese; (5) possess and proficiently use a smartphone; and (6) consent to participate. Patients with (1) severe physical or mental health conditions, or (2) a history of psychotic illness or (3) severe motion sickness or vertigo in the past will be excluded.

### Sample size and recruitment

The primary outcome of the sick role adaptation in this study was used to calculate the effect size. Given the little published data on the effectiveness of VR-assisted CBT on the sick role adaptation among cancer patients, the sample size was calculated using PASS 15.0 based on a prior study in which a CBT intervention was delivered to elderly inpatients and yielded a s statistically significant improvement in the sick role adaptation. The mean score of the sick role dimension of the intervention group was (4.8 ± 1.2) and (6.6 ± 1.5) of the control groups. A sample size of 23 participants per group, assuming a more moderate effect size of 0.5, is predicted to provide the study with 95% power at a 1% level of significance to detect an effect size of at least 0.5 for the study's primary outcome of the sick role adaptation following the intervention. There will be a need for a total of 60 participants, with 30 in each arm, assuming a 20% attrition rate.

Eligible participants will be recruited through poster advertisements in wards and referrals from physicians. Then they will be approached by a research nurse who will distribute information sheets detailing the VR-CBT app and relevant consent forms. Prior to randomization, baseline data will be collected after receiving written consent. Data for follow-up will be collected at 1, 2 and 3-month after the completion of the 7-week sessions to examine the sustainability of the effects. The recruitment of participants will be completed by December 2023. Once recruited, patients will be randomly assigned to the VR-CBT group or AC group.

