### Data analysis

Data will be analyzed using IBM SPSS 26.0 (IBM Corp.). Demographic data will be described and presented with appropriate statistics, including frequency distributions, means with standard deviations, medians with interquartile ranges. In the case of skewed variables, appropriate transformations will be applied prior to their inclusion in the inferential analysis. The outcome analysis will adhere to the intention-to-treat principle. The homogeneity of baseline characteristics between the two groups will be assessed using appropriate statistical tests including independent *t*- test, chi- squared test or Fisher's exact test. The study will apply the generalized estimating equations model adjusting for specific covariates (sex, age, monthly income per capita, family history of cancer, stage of cancer, and time), to compare the changes in each outcome variables between the two groups across different time points. Multiple imputation will be adopted to handle missing data. All statistical tests employed in this study will be two-tailed, with a significance level set at 0.05.

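### The stated 95% power for an effect size of 0.5 with 23 per group is wrong: a simple two-group comparison has about 17% power at the 1% level and 38% at the 5% level

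*Protocol article*

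**What the plan says.** Under Sample size and recruitment, the protocol names sick role adaptation as the outcome used for sizing and PASS 15.0 as the software. It cites a prior CBT study in elderly inpatients: "The mean score of the sick role dimension of the intervention group was (4.8 ± 1.2) and (6.6 ± 1.5) of the control groups". It then moves to a smaller effect: "A sample size of 23 participants per group, assuming a more moderate effect size of 0.5". The claim made for this group size is "95% power at a 1% level of significance", and the same sentence ties that claim to a primary-outcome effect no smaller than 0.5. With 20% attrition this becomes 30 per arm, 60 in total.

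The section mentions no repeated measurements, no correlation between time points and no variance reduction from covariates.

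Under Data analysis, the outcomes are compared across time points with generalized estimating equations (GEE), adjusted for listed covariates. The testing rule is: "All statistical tests employed in this study will be two-tailed, with a significance level set at 0.05".

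**The concern.** A standardised effect of 0.5 is conventionally moderate, and a trial with 23 evaluable patients per arm is small. Power of 95% at a 1% level for that combination looks implausible at first sight. All four quantities (group size, effect, level, power) are printed, so the statement can be tested without any outside source.

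This sentence is the only justification given for the size of the trial, and it concerns the primary outcome. A reader who trusts it would think a moderate effect almost certain to be detected, and could take a non-significant result as near-proof that no such effect exists. The wording also suggests that the planners stepped back from an optimistic prior result. If 23 came from that prior result, no such caution was built in.

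A second, smaller matter is that the trial is sized at 1% but tested at 5%, with no explanation.

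**Working it through.** **Inputs from the protocol.** 23 per group; effect 0.5; level 1%; power 95%; prior-study scores 4.8 (SD 1.2) and 6.6 (SD 1.5); attrition 20%; 30 per arm; 1:1 allocation (Randomization and blinding); two-tailed tests at 0.05 (Data analysis).

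**Method.** Two-sample t-test with n per group, noncentrality d × √(n/2) and 2n − 2 degrees of freedom. Power is the probability that the noncentral t exceeds the two-sided critical value. As a hand check, the normal approximation is n = 2(z₁₋α/₂ + z_power)² / d².

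**1. The plan's own statement: n = 23, d = 0.5.** Noncentrality = 0.5 × √11.5 = 1.70.

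| n per arm | Power at 1% | Power at 5% |
|---|---|---|
| 23 | 17.3% | 38.2% |
| 24 (30 less 20%) | 18.3% | 39.6% |
| 30 (no losses) | 24.4% | 47.8% |

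The stated 95% is not reproduced.

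**2. Group size needed for 95% power at d = 0.5.**
- 1%: 2 × (2.576 + 1.645)² / 0.25 ≈ 143 by the normal formula; 145 by the t-test.
- 5%: 2 × (1.960 + 1.645)² / 0.25 ≈ 104 by the normal formula; 105 by the t-test.

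**3. Where 23 may come from.** Pooled SD = √((1.2² + 1.5²)/2) = 1.358, and d = (6.6 − 4.8)/1.358 = 1.325. At two-sided 1% and 95% power the t-test needs 22.02, hence 23 per group. With 22 the power is 94.98%; with 23 it is 96.0%. So the printed group size, level and power all agree with the unmoderated prior-study effect.

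**4. Other readings of the sentence, n = 23.**
- One-sided, d = 0.5: 24.7% at 1%, 51.0% at 5%.
- 0.5 read as Cohen's f (d = 1.0), two-sided: 75.4% at 1%, 91.2% at 5%. Only a one-sided 5% test takes this reading to 95% with 23 per group, and that contradicts both the 1% level and the two-tailed rule.

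**5. Attrition.** 23/0.8 = 28.75, so 29 per arm suffices and 30 covers it. 30 × 0.8 = 24 evaluable per arm. This step is sound.

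**6. Detectable effect with 24 per arm at two-sided 5%.** 0.83 SD with 80% power; 1.06 SD with 95% power.

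**7. Allowance for repeated measures.** The correlation is not in the protocol, so a range is assumed: one common correlation ρ among baseline and the three follow-ups, a constant effect of 0.5 SD, 24 per arm, and the mean of the three follow-ups adjusted for baseline. Relative variance = (1 + 2ρ)/3 − ρ².

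| Assumed ρ | Variance factor | Power at 1% | Power at 5% |
|---|---|---|---|
| 0.3 | 0.443 | 47% | 72% |
| 0.5 | 0.417 | 50% | 75% |
| 0.7 | 0.310 | 66% | 86% |
| 0.8 | 0.227 | 82% | 94% |
| 0.9 | 0.123 | 98.5% | above 99% |

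The normal approximation gives slightly higher values (70% and 88% at ρ = 0.7). The range for ρ from 0.3 to 0.7 is therefore roughly 47–70% at 1% and 72–88% at 5%.

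**The case against.** The strongest reply is that a t-test at one time point is not the planned analysis. The protocol plans a GEE model over several time points with covariates, tested at 5%. A reader might infer from the 17% that this is the true power of the trial, or that the trial would miss a 0.5 SD effect more often than not. The documents do not support either reading. Power under the planned model depends on correlations that are not stated, and a favourable version (baseline-adjusted mean of three follow-ups, ρ = 0.5) has about 75% power at 5%. This limits the consequence but does not rescue the sentence, which claims 95% at 1% and mentions no repeated measures. The listed covariates also do not include the baseline score. Under the same assumptions with ρ = 0.5, a mean change from baseline gives only 30% at 1% and 55% at 5%.

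A reader might also conclude that 0.5 was never used. The match with 1.33 SD is close, but the software inputs are not shown, so this remains a probable explanation.

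Nor do the two levels amount to two competing decision thresholds. Only the data analysis section sets a testing rule ("two-tailed, with a significance level set at 0.05"), and sizing at a stricter level than is tested can be a deliberate, conservative choice. What stands is an unexplained mismatch.

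Finally, nothing in the protocol says that a null result will be read as excluding a moderate effect. That is a risk created by the wording, not a stated intention.

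**Conclusion.** The sentence is wrong as written. For a two-group comparison of means, 23 per group, an effect of 0.5 SD, a 1% level and 95% power cannot all hold. Power is about 17% at two-sided 1% and 38% at two-sided 5%, and the requirement for 95% is about six times the stated group size at 1% (145/23 = 6.3) and between four and five times at 5% (105/23 = 4.6). These results use only figures printed in the protocol and a standard t-test.

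The attribution of 23 to the prior-study effect is a strong inference. Power under the planned GEE model is unknown. On the assumptions shown it exceeds the t-test figure, yet 95% at 1% is reached only with a correlation between 0.8 and 0.9, which the protocol does not claim. The 1% versus 5% mismatch is real but secondary.

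**What to change.** 1. Check the PASS record and restate the sentence with the effect size actually used, which appears to be about 1.33 SD at two-sided 1% and 95% power.
2. State what the trial can detect at the level it will test: with 24 evaluable per arm and two-sided 5%, a simple two-group comparison has about 40% power for 0.5 SD and 80% power for about 0.83 SD. If higher power is claimed through the repeated-measures model, state the assumed correlation and the baseline adjustment.
3. Use the same significance level in the sample size and data analysis sections, or explain why they differ.
4. Add that a non-significant result does not exclude a moderate effect.

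These are changes of wording and need no extra patients. The cost is that the stated power becomes much less favourable.

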### Randomization and blinding

Participants will be assigned to the VR-CBT group or AC group using a stratified randomization, with an allocation ratio of 1:1, to ensure the equal distribution in colon cancer and rectum cancer patients throughout the recruitment period. A random sequence of grouping identifiers will be produced in advance using computer-generated random numbers by a researcher who does not participate in the trial and determine the eligibility of the subjects. According to the enrollment order and the associated group identifier in the previously created random sequence list, the group allocation for each participant will be distributed consecutively. Because of the nature of psychological interventions adopted in the study, it is difficult to conceal participants and the researchers who administer the intervention, researchers who will assess the outcomes will be blinded solely and not be notified of the group status of the participants.

## Intervention

### The attention control intervention

Threats to internal validity in RCTs will be reduced by the use of an AC group [36]. Participants assigned to the AC group will receive 7-week regular health consultations through WeChat as an attention control in addition to standard care by an experienced clinical nurse from the research setting. The nurse will contact participants in the AC group weekly from 1 week pre-surgery to 6 weeks post-surgery, to ask about recent health status using standardized questions such as ‘How do you feel today?’ ‘How is your appetite?’ and ‘How was your sleep last night’ and give general advice.

### The VR-CBT intervention

Participants in the VR-CBT group will be asked to complete a 7-sessions VR-CBT via a mobile app added onto standard care. We believe that this format will be more acceptable and available for working-age adults with CRC. The intervention is based on CSM targeted for negative emotions, irrational illness cognition, maladaptive coping strategies and supported by the use of CBT techniques during the intervention. According to psychological characteristics of patents in perioperative and rehabilitation stage, the weekly intervention will sequentially provide techniques of negative emotion adjustment, illness cognition reconstruction, and effective coping behaviors as the sick role at two different stages, from pre-surgery to 6 weeks post-surgery. Each session is estimated to take 40 min to complete. Patients will be allowed to repeat sessions at any time if they want within the intervention weeks. Figure 2 shows the overview of intervention targets, sessions in perioperative stage and rehabilitation stage, and adopted VR techniques.

